## **11.2 Follow-up Schedule (10/1/96)**

**11.2.1** Every 3 months for the remainder of the first year.

**11.2.2** Every 4 months during the second year.

**11.2.3** Every 6 months for years 3-5 then annually the remainder of the patient's life.

- 11.2.4** A bone scan will be performed on any patient who presents with complaints of bone pain that cannot be attributed to any intercurrent disease. Discretionary plain films may be needed to evaluate lesions seen on bone scan to confirm the diagnosis of metastatic disease.
- 11.2.5** The patient will be asked whether he is able to achieve an erection and/or ejaculation and if he is able to have sexual relations. This assessment must be done prior to the start of any treatment, prior to the start of radiation therapy (*Arm 1*), at the end of treatment and at each follow-up visit through year 2.
- 11.2.6** The Sexual Adjustment Questionnaire (*SAQ*) will be given to the patient to complete every three months for the remainder of the first year, then every four months in the second year. No *SAQ* will be required beyond the second year. An additional questionnaire will be completed prior to starting XRT but after the induction phase of hormones is completed.
- 11.2.7** Because an endpoint in this study is tumor clearance and local control, a biopsy of the prostate will be obtained at 24 months following completion of radiation therapy.

### **11.3 Measurement of Effect/Response**

Prostate/prostate tumor dimensions in cm should be calculated from physical exam and must be recorded on the diagrams found on the data collection forms for initial and follow-up evaluation of the patient. After study entry, disease activity evaluations will be made and recorded using the following criteria:

- 11.3.1** No Evidence of Disease (NED): no clinical evidence of disease on digital rectal examination.
- 11.3.2** Equivocal Disease (ED): this rating will be assigned under the following two circumstances.
- If abnormalities are present on the prostate digital rectal examination but are thought to be abnormal due to treatment and felt not to represent tumor.
  - If clinical evidence of residual tumor is present but this has regressed from a previous examination (*initial registration*)
- 11.3.3** Progressive Disease (PD): this rating will be assigned when there is clinical evidence in the prostate gland of disease progression or recurrence measured by a 25% or greater increase in the product of the two largest perpendicular diameters of the prostate. Only those patients with progressive disease on digital rectal examination will be scored as digital rectal examination failure. The time of failure will be backdated to the first occurrence of equivocal disease after a prior normal examination or to the end of radiation therapy treatment if a normal digital rectal examination was never achieved.
- 11.3.4** Time to Disease-Free Survival: Time to the disease-free survival will be measured from the date of randomization to the date of documentation of progression (local progression, distant failure, and PSA failure) or until the date of death (*from other causes*). (7/14/08)
- 11.3.5** Time to Complete Response (CR): Time in months from randomization to documentation of no evidence of disease (*NED*).
- 11.3.6** Time to PSA Failure: Time in months from randomization to PSA failure as defined below:
- 11.3.6.1** A rise in PSA on at least two consecutive occasions above the nadir. In patients who have been declared a PSA relapse, every effort should be made to withhold further Rx until clinical relapse is evident. When this impossible, the site of failure should be ascertained before instituting further Rx. This may necessitate a bone scan, CT and prostate biopsy.

- 11.3.6.2** The rises in PSA must exceed 1ng/ml above the nadir.
- 11.3.6.3** Failure of the PSA to reach 4 ng/ml or less at 18 months.
- 11.3.7** Time to Second PSA Failure:  
The time from randomization to second PSA failure as defined below  
(*after institution of relapse therapy*):
- 11.3.7.1** A rise in PSA on at least two consecutive cases above the nadir (*after initiation of relapse therapy*).
- 11.3.7.2** The rises in PSA must exceed 1 ng/ml above the nadir.
- 11.3.7.3** Failure of the PSA to reach 4 ng/L or less at 18 months.
- 11.3.8** Time to Local Progression: The time to progression will be measured from the date of randomization to the date of documented local progression as determined by clinical exam.
- 11.3.9** Time to Distant Failure:  
The time to distant failure will be measured from the date of randomization to the date of documented metastatic disease.
- 11.3.10** Time to Overall Survival: (7/14/08)  
The time to overall survival will be measured from the date of randomization to the date of death due to any cause. All patients will be followed for survival. Every effort should be made

to document the cause of death. Post-mortem examination will be carried out when feasible and a copy of the final autopsy report sent to RTOG.

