### 11.3.11 Time to Disease Specific Survival: (7/1/97) (7/14/08)

The time to disease specific survival will be measured from the date of randomization to the date of the following events.

- a. The following will be considered as endpoints in assessing disease specific survival (DSS), i.e., events:
  - Death certified as due to prostatic cancer.
  - Death due to complications of treatment, irrespective of the status of malignancy.
  - Death from unknown causes with active malignancy (*clinical or biochemical progression*).
  - Death from unknown causes with previously documented relapse (*either clinical or biochemical*).
- b. The following will be considered as events that may be related to death from prostate cancer. They will be added into the previous definition for a separate analysis.
  - Death from unknown causes without reported relapse.
  - Death from other causes with previous documented relapse (*either clinical or biochemical*) but inactive at the time of death.

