### **13.2.2 Secondary Endpoints**

**13.2.2.1** Disease-specific survival (See section 11.3.11)

**13.2.2.2** Local progression (See section 11.3.8)

**13.2.2.3** Distant failure (See section 11.3.9)

**13.2.2.4** Freedom from PSA failure (See section 11.3.6)

**13.2.2.5** Freedom from second clinical relapse (local progression and/or distant failure)

**13.2.2.6** Freedom from second PSA relapse (See section 11.3.7)

**13.2.2.7** Disease-free survival (See section 11.3.4)

**13.2.2.8** Prostate re-biopsy at two years

**13.2.2.9** Effect on sexual function (See section 11.3.12)

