#### **13.4.2 Time to Failure of Secondary Survival Endpoints**

The time to disease-free survival (DFS) will be measured from the date of randomization to the date of events (see section 11.3.4). The survival distribution of DFS will be estimated by the Kaplan-Meier method. We want to show that the hazard rate of Arm 1 ( $\lambda_1$ ) will be lower than that of Arm 2 ( $\lambda_2$ ) in the DFS distribution. This hypothesis will be tested using a log-rank test statistic at a significance level  $\alpha = 0.025$ . The treatment effect on the other types of failure (disease-specific survival, local progression, distant failure, PSA failure, second clinical relapse,

second PSA relapse) may impact the observable measures of outcomes and other competing risks may dilute the sensitivity. We will use the cause-specific hazard rate approach to consider the competing events. Freidlin and Korn showed that the cause-specific hazard rate approach is better than other approaches (for example, the cumulative incidence method in most cases. The log-rank test on the times to the specific type of failure, which considers the presence of competing events, will be used to test whether the survival/failure rates of these secondary endpoints in Arm 1 are better than that of Arm 2 for each hypothesis at a significance level of 0.025. In this approach, patients who experience other failure first are censored. To analyze whether treatment effect is independently associated with secondary survival endpoints while adjusting for other factors, a Cox proportional hazards regression model was used for DFS and Fine and Gray's regression model were used for the other types of secondary survival endpoints. Both unadjusted and adjusted hazard ratios and the respective 95% confidence interval will be computed. At least the treatment arm, the stratification variables (PSA, grade, nodal status), age, and race (as appropriate) will be adjusted for in this analysis.

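### The DFS definition in Section 11.3.4 restricts its death component to other causes, which conflicts with how the protocol uses that term and with the DFS analysis in Section 13.4.2

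*Protocol*

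**What the plan says.** Section 11.3.4, dated 7/14/08, measures DFS from randomization to documented local, distant or PSA failure, or "until the date of death (*from other causes". No other section widens this. The secondary endpoint list gives only "Disease-free survival (See section 11.3.4", and Section 13.4.2 gives "The time to disease-free survival (DFS) will be measured from the date of randomization to the date of events (see section 11.3.4".

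For overall survival, Section 11.3.10 carries the same 7/14/08 date and runs "from the date of randomization to the date of death due to any cause".

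Section 11.3.11, on disease-specific survival (DSS), sorts deaths by cause. Among the DSS events it lists "Death certified as due to prostatic cancer", together with deaths from complications of treatment. Among deaths that enter only a separate, wider analysis it lists "Death from unknown causes without reported relapse" and, as its own item, "Death from other causes with previous documented relapse".

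Section 13.4.2 tests DFS by log-rank at 0.025, estimates it by Kaplan-Meier and models it by Cox regression. For the remaining failure endpoints, including DSS, it brings in competing events, cause-specific hazards with censoring at an earlier failure of another type, and Fine and Gray regression.

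**The concern.** In a DFS endpoint the death component normally needs no cause, because a man who has died is no longer alive and disease-free. Here a qualifier is attached, and this protocol uses the qualifying term for one particular class of deaths. If an analyst applies that class, some deaths fall outside DFS: men certified as dying of prostate cancer, and men dying of unknown causes, where no progression had been recorded. Deaths from complications of treatment are unclear as well.

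Under Kaplan-Meier and log-rank, a death that is not an event can only be a censoring. That censoring would be informative: a prostate-cancer death with no recorded progression most likely means that progression was missed, not that the man's outlook matched that of those still at risk. DFS would also come to depend on cause-of-death attribution, which Section 13.3 describes as difficult for prostate cancer. Two analysts following the same text could code the same death differently in an endpoint that is formally tested.

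**Working it through.** **1. What the term means elsewhere in the protocol**

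- Section 11.3.11 treats prostate-cancer, treatment-complication, unknown-cause and other-cause deaths as separate items.
- The cause-of-death table in Section 13.6 has separate Prostate, Other and Unknown columns.
- Section 13.3 uses the term for mortality not due to prostate cancer. Its split is two-way (14 of 46 deaths to prostate cancer, the remaining 32 of 46 to other causes), so it separates out prostate-cancer deaths but says nothing about unknown-cause deaths.
- Section 11.3.10 uses any-cause wording where all deaths are meant.

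**2. How each death without documented progression is classed**

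| Cause of death | DSS (11.3.11) | DFS, if the term is a cause-of-death class | DFS, if it means any cause other than progression |
|---|---|---|---|
| Certified prostate cancer | event | not an event | event |
| Complication of treatment | event | unclear | event |
| Unknown | separate wider analysis only | not an event | event |
| Other | not an event | event | event |

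The first row is the incoherent one: on the narrower reading, a man has a DSS event and no DFS event. The second row may share the problem.

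**3. Which reading the analysis section fits**

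If the deaths in the first and third rows are not DFS events, they are competing events for DFS. Section 13.4.2 makes competing-event provisions for the other failure endpoints and none for DFS. That fits the last column, not the one before it.

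**4. Scale**

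The protocol gives no design figure for DFS. The only death count available as a scale is the 716 deaths for overall survival in Section 13.4.1, and that figure reproduces:

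- Hazard ratio = ln(0.67)/ln(0.60) = 0.784.
- Freedman: (1.960 + 1.282)² × (1.784/0.216)² ≈ 717.
- Schoenfeld: 4 × (1.960 + 1.282)² / (ln 0.784)² ≈ 710.

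The DFS wording does not affect it.

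Cause-of-death shares come from the RTOG 77-06 (T1/T2, combined) row of the table in Section 13.6, where 76 + 165 + 17 = 258:

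- Prostate cancer: 76/258 = 29.5%; × 716 ≈ 211.
- Unknown: 17/258 = 6.6%; × 716 ≈ 47.
- Other: 165/258 = 64.0%; × 716 ≈ 458.
- Prostate cancer plus unknown: 93/258 = 36.0%; × 716 ≈ 258. (That this equals the table's denominator is a coincidence.)
- By Gleason group, the combined share is (49 + 14)/186 = 33.9% for scores 2-6 and (25 + 3)/62 = 45.2% for scores 7-10.

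These are ceilings. Only deaths with no earlier documented local, distant or PSA failure would be lost, and the protocol does not give that fraction. For illustration, assumed fractions of 5%, 10% and 25% of the 258 deaths give about 13, 26 and 65.

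**The case against.** The best defence is grammatical. Within the sentence in 11.3.4, the only thing that *other* can refer back to is progression. On that reading the parenthesis merely marks deaths not already captured by progression, and every death counts. The table in 13.6 describes earlier trials in an overview dated 7/1/97, and 11.3.11 serves a different endpoint, so neither formally defines terms for 11.3.4. The plain DFS analysis in 13.4.2 supports this inclusive reading.

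Much of this stands. The inclusive reading is plausible and may be what was meant. It does not settle the matter, because the text does not state it, the protocol's own use of the term runs against it, and any-cause wording was used in 11.3.10 under the same date.

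It does rule out three stronger readings that a reader might infer:

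- **That the plan orders these deaths to be censored.** No sentence says so for DFS. The statement in 13.4.2 about censoring at another failure concerns the other endpoints.
- **That 47, or 258, deaths would be lost.** Those figures include men with earlier documented failure, who are already DFS events. Section 11.3.11 lists unknown-cause deaths after documented relapse as a category of their own. PSA failure counts towards DFS and PSA is required at least every 6 months, so many prostate-cancer deaths should follow a recorded event.
- **That the loss favours one arm.** The follow-up schedule in Section 11.2 is the same for both arms, and the protocol gives no figure for how completely progression is documented in either.

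**Conclusion.** The point holds as a conflict in the definition of a secondary endpoint. The death qualifier in 11.3.4, read with the protocol's own vocabulary, leaves out prostate-cancer and unknown-cause deaths without documented progression, and arguably treatment-complication deaths. The analysis in 13.4.2 is written as if all deaths were included.

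The number of deaths at issue cannot be derived from the protocol. The upper bounds of about 47 unknown-cause and 211 prostate-cancer deaths assume that the 77-06 shares carry over to 716 deaths in this trial. The actual loss depends on an unstated fraction and is probably small, as is any effect on the DFS hazard ratio. Overall survival, its 716-death target and its power are unaffected. This is a minor correction, worth making because DFS is formally tested at 0.025 and its event rule should not turn on cause-of-death attribution.

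**What to change.** In Section 11.3.4, replace the qualified death component so that DFS ends at documented local progression, distant failure or PSA failure, or at death from any cause, whichever comes first. This matches the wording of 11.3.10 and the analysis already set out in 13.4.2, so neither of those sections needs to change.

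The cost is one phrase. All patients are already followed for survival under 11.3.10, so no new data are needed, and no sample size, event count or significance level moves.

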## 1.0 INTRODUCTION

- 1.1 Endocrine hormonal therapy was introduced by Huggins in 1941 and is based on the dependence of prostatic epithelial cells and prostatic adenocarcinoma cells on androgenic hormones. Androgen deprivation by orchidectomy, estrogens or other antiandrogens can produce dramatic and often prolonged improvement in a large percentage of patients.
- 1.2 In early stage prostate cancer, there is ample evidence that external beam radiation therapy is effective in the local control and cure of a large proportion of patients (*5 year disease free survival approximately 80% and at 10 years approximately 60%*). Despite these results, approximately 30% of patients who are in complete clinical remission will have abnormal PSA's suggesting that these patients will eventually fail.
- 1.3 The use of a combination of cytoreductive hormonal therapy prior to and during radiation therapy has been the subject of several publications. The recently completed RTOG study (RTOG 86-10) of locally advanced disease has demonstrated an improvement in disease-free survival (*at 2 years 76 % for hormones plus radiation therapy versus 62% for radiation therapy alone*), and in addition a delay in relapse of approximately 9-12 months. There was also an improvement when PSA failure (*defined as a PSA greater than 4 g/L at 1-2.5 years*) was included. Since this study predated the introduction of PSA assays, data was not collected before treatment in all patients and, in addition, follow-up PSA data collection was incomplete.
- 1.4 Experimental data indicates that differentiated prostate cells undergo cell death in the absence of androgens and that there is a significant killing of their stem cells. It has been postulated that the presence of androgens may suppress a cell death gene. The earliest apparent signs of morphologic change exhibited by the dying cells is described by a process called apoptosis. The cytoreductive effects of androgen deprivation may also result in the killing of a significant portion of prostate cancer stem cells and thus may contribute to the ability of radiation therapy to eradicate all the tumor stem cells at the primary site. The ability of androgen deprivation to improve local control with radiation therapy may actually be greater in small tumors than large tumors as the initial tumor stem cell population may be smaller and because smaller tumors are often more well differentiated.

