## **11.0 PATIENT ASSESSMENTS**

### **11.1 Study Parameters (10/1/96, 7/1/97, 9/8/98, 11/13/00)**

| Parameter      | Pretreatment | At start of XRT | At end of XRT | Follow-up |
|-----------------------|---------------------|------------------------|----------------------|------------------|
| History & Physical    | X                   | X(b)                   | X                    | X                |
| Karnofsky Status      | X                   | X(b)                   | X                    | X                |
| Sexual Status         | X                   | X(b)                   | X                    | X                |
| Chest X-ray           |                     |                        |                      | X(a)             |
| Bone Scan             | X                   |                        |                      | X(a)             |
| CBC, alk. phos.       | X                   | X(b)                   | X                    | X(e)             |
| ALT                   | X                   | X(b,f)                 | X(b)                 | X(c)             |
| Serum Testosterone    | X                   |                        | X                    | X(d)             |
| Lymph Node Assessment | X                   |                        |                      | X(a)             |
| PSA                   | X                   | X(b)                   | X                    | X(g)             |
| Prostate Biopsy       | X                   |                        |                      | at 24 months     |

- As indicated
- Only in patients assigned to receive drug treatment, Arm 1.
- If abnormal following administration of drugs.
- Serum testosterone will be repeated at the time of the first follow-up in all patients. If abnormal, repeat until it returns to the normal range or at 2 years, whichever comes first. For patients assigned to Arm 1, serum testosterone levels will be done when Zoladex is terminated and at 6 and 12 months post termination.
- CBC is done at every followup for 2 years after end of treatment; alkaline phosphatase is performed yearly.
- Monthly during hormone therapy. If liver functions rise to  $\geq 2 \times$  normal, flutamide will be discontinued and [name] notified.

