## **13.3 Sample size and accrual (7/14/08)**

**As of July 1, 1997, the sample size is 1980 (See section 13.7).**

*TAS* is known to lower PSA but time to initial PSA failure may not be a good indicator of ultimate clinical outcome. If neoadjuvant *TAS* is successful, there should ultimately be a positive impact on cause-specific survival. Because of the expected mortality due to other causes in this population, an improvement in cause-specific survival may be difficult to detect if overall survival were used as the primary endpoint. Clearly identifying deaths due to prostate cancer is difficult because metastasis is usually to the bone rather than to a vital organ.

The primary endpoint for this trial upon which sample size is based is defined to be closely associated to death due to prostate cancer. Review of causes of death by the study chair will be necessary.

The following will be considered treatment failures:

1. Death certified as due to carcinoma of the prostate.
2. Cancer associated death.
3. Death due to complications of treatment irrespective of the status of the cancer.
4. Progressive metastatic disease while on any antitumor therapy.
5. Rising PSA while on any antitumor therapy.

Average failure rates were obtained from other datasets with the recognition that they may not be identical with what might be expected from this population.

Death rate: The death rate from early stage prostate patients from RTOG 77-06 had an average annual death rate of 0.045. Fourteen of the 46 reported deaths were categorized as due to prostate cancer. The prostate cancer death rate and other cause death rate were found by multiplying 0.045 by 14/46 and (46-14)/46.

Rate of first failure: This was taken to be 0.12 (*communication [name]*).

Rate of second failure while on hormonal therapy: This was taken to be 0.24 (*communication [name]*).

The goal of the trial is to be able to detect a lowering of the failure rates by 33% with 90% power using a two-sided test. Using methods described by Lakatos, **a total of N=670 patients are required** to be accrued uniformly over three years and followed for three additional years before final analysis of treatment failure. This includes an estimate of 10% unevaluable patients. The expected numbers of events on the two arms at the time of final analysis are 71 and 39.

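### First PSA failure is judged against a nadir that in Arm 1 may be set under castrate testosterone, so PSA failure and DFS can differ between arms with no difference in tumour control

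*Protocol*

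**What the plan says.** Protocol 11.3.6 sets one rule for both arms. The endpoint is "Time in months from randomization to PSA failure as defined below". The first criterion is "A rise in PSA on at least two consecutive occasions above the nadir", qualified by "The rises in PSA must exceed 1ng/ml above the nadir". A further criterion is "Failure of the PSA to reach 4 ng/ml or less at 18 months". No start point is given for the nadir, and nothing addresses values taken under TAS or while testosterone is recovering.

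Under 11.3.4, DFS runs to "documentation of progression (local progression, distant failure, and PSA failure", or to death. Section 13.4.2 tests DFS, and PSA failure in its own right, by log-rank at 0.025 with the alternative that Arm 1 is better. Both are listed objectives in 2.2.1.

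Testosterone is collected. Note d to the table in 11.1 has it repeated at first follow-up in all patients and, if abnormal, until normal or 2 years. It adds: "For patients assigned to Arm 1, serum testosterone levels will be done when Zoladex is terminated and at 6 and 12 months post termination". These values do not enter 11.3.6. Section 13.3 acknowledges that TAS lowers PSA and that "time to initial PSA failure may not be a good indicator of ultimate clinical outcome".

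**The concern.** PSA depends on androgen as well as on tumour. Only Arm 1 has its androgen removed and then restored within the period in which the nadir is likely to be established. A rule that treats every rise from the lowest value alike cannot separate returning testosterone from regrowth.

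Two distortions follow, with opposite signs. A man whose nadir was recorded under suppression may meet the rule as testosterone returns, which counts against TAS. Conversely, Arm 1 starts radiotherapy two months later, and suppression may persist for a time after the last injection. True failures may then surface later on a clock that starts at randomization, which counts in favour of TAS.

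At stake is the reading of PSA failure and DFS: a difference between arms, or the absence of one, could not be attributed to tumour control. At the margin DSS is touched too, because 11.3.11 uses biochemical relapse to decide whether some deaths from unknown causes count.

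**Working it through.** **1. Can an Arm 1 nadir be set under suppression?** TAS lasts about 112 days (7.1.4, 7.2.4). Testosterone falls to the castrate range (7.1.5, 7.3.1), and 7.3.1 calls the suppression reversible. The table in 11.1 schedules PSA at the start of radiotherapy in Arm 1 only, after two months of TAS, and at the end of radiotherapy in both arms. Arm 1 therefore has values under TAS that can be the lowest recorded. By contrast, 11.3.7.1 does anchor the nadir for second PSA failure, to the start of relapse therapy.

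**2. The rule on two invented PSA series (ng/ml).**
- Arm 1: 0.2, 0.6, 1.3, 1.4, then flat. Nadir 0.2; threshold 0.2 + 1 = 1.2. The values 1.3 and 1.4 are consecutive rises and both exceed 1.2, so this is a failure.
- Arm 2: 4.0, 2.5, 1.8, 1.4, then flat. Nadir 1.4 and no rise, so this is not a failure.

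The two men have the same PSA from then on and opposite outcomes. The Arm 1 man clears the threshold by only 0.1 and 0.2.

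**3. How much delay is documented?** Radiotherapy of 37 fractions at four to five a week takes 37/5 = 7.4 to 37/4 = 9.25 weeks, about 52 to 65 days. Arm 2 starts within 21 days, so it finishes between about day 52 and day 21 + 65 = 86. The first three-monthly visit (about 91 days later) falls between about day 143 and day 177, after day 112. Time on drug is thus mostly time in which Arm 2 has no post-radiotherapy follow-up PSA either. The documented offset is the two months in radiotherapy start. Any persistence of suppression beyond day 112 is not quantified in the protocol.

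**4. Size under no true effect.** The protocol gives no event count or power for PSA failure or DFS, so there is no planned figure to reproduce.

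Inputs from the protocol: 1779 evaluable men, 1:1, five years' accrual plus eight years' follow-up (13.8.2); first-failure rate 0.12 per year in both arms (13.3); other-cause death 0.045 × 32/46 = 0.0313 per year (13.3).

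Assumptions: the delay d is added to every Arm 1 failure time; a fraction f of Arm 1 men fail falsely at 0.6-1.3 years.

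Statistic: z = (O − E)/√V for Arm 1, with TAS called better if z < −1.96 and worse if z > 1.96. There were 1500 runs per row, so the Monte Carlo standard error at 13.7% is √(0.137 × 0.863/1500) = 0.9 points.

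| Delay d | Rebound f | TAS falsely better | TAS falsely worse | Rate ratio |
|---|---|---|---|---|
| none | 0 | 2.5% | 2.7% | 1.00 |
| 2 months | 0 | 5.9% | 0.6% | 0.98 |
| 112 days | 0 | 13.7% | 0.1% | 0.96 |
| 6 months | 0 | 29.8% | 0.1% | 0.93 |
| none | 2% | 1.2% | 6.5% | 1.02 |
| none | 5% | 0.0% | 16.7% | 1.06 |
| none | 10% | 0.0% | 55.5% | 1.12 |
| 112 days | 5% | 1.5% | 3.5% | 1.01 |
| 112 days | 10% | 0.1% | 24.9% | 1.07 |
| 6 months | 5% | 5.3% | 0.9% | 0.98 |

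A repeat gave 6% (2 months), 15% (112 days), 17% and 53% (5% and 10% rebound), and 1.8% / 4.5% for 112 days plus 5%. A variant with 890 men per arm, death rate 0.045, an assumed follow-up of 5.5-10.5 years, rebound at 9-18 months and 400 runs gave 16% (4 months), 28% (6 months), and 19% and 56% (5% and 10% rebound).

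**The case against.** The primary endpoint is overall survival, 13.3 already warns about first PSA failure, and local progression, distant failure, DSS and re-biopsy are separate endpoints. The two-rise and 1 ng/ml requirements filter small rebounds. All of this stands, and it limits the point to the interpretation of secondary endpoints. It does not remove the point, because the warning in 13.3 is not carried into 11.3.4, 11.3.6 or 13.4.2.

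A reader might infer more than the documents support:

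- *That the Arm 1 nadir always falls at the end of TAS.* Arm 1 also receives radiotherapy, and PSA may fall further afterwards.
- *That no Arm 1 man can show a PSA rise on drug.* Section 13.3 lists a rising PSA during antitumor therapy among failures, and 10.5 studies hormone resistance.
- *That the protocol documents a masking period of 9-12 months.* Section 1.3 reports "a delay in relapse of approximately 9-12 months", but from a study in locally advanced disease that predated PSA assays, and as a benefit. The title describes TAS as cytoreductive and cytostatic, so a real delay is part of the hypothesis. Entering 9 or 12 months as artefact gives 55% or 79% falsely better, but those inputs have no support as masking.
- *That TAS would formally be declared worse.* The test in 13.4.2 is directional. A spurious harm would show in the reported hazard ratio and confidence interval, not as a conclusion of that test.

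It is also tempting to rewrite the main definition so that Arm 1 rises must be re-confirmed from a post-recovery baseline. That raises the bar essentially in Arm 1 alone and can lose true failures in men who die, are censored or start relapse therapy before confirmation.

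**Conclusion.** The point holds for PSA failure and DFS. A common nadir rule with no start point and no reference to testosterone lets a passing drug effect on PSA, or the later radiotherapy start, move both endpoints without any difference in tumour control. Either artefact alone raises the 2.5% error rate materially at the values tried, while 112 days of delay with 5% rebound nearly cancels.

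The delays, rebound fractions and rebound timing are assumptions. The simulation also treats every first failure as subject to the delay, which overstates that effect to the extent that first failures are clinical. Neither the sign nor the size of the net bias can be derived from the protocol, and a reader should not infer one. Nor is the problem beyond repair: the PSA and testosterone values needed to examine it are already being collected. Overall survival is untouched.

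**What to change.** Keep 11.3.6 as the main definition and amend 13.4.2:

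(a) Report clinical DFS (local progression, distant failure or death, without PSA failure) beside DFS. State that no DFS benefit or harm will be claimed if it rests on the PSA component alone.

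(b) Add a sensitivity analysis of PSA failure and DFS, applied identically to both arms. A rise that begins before documented testosterone recovery counts only if it continues after recovery. Men who die, are censored or start relapse therapy before that can be confirmed stay failures at the date given by 11.3.6.

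The cost is amended wording and a few extra time-to-event analyses on data already collected, with no change to treatment or visits. Clinical DFS will have fewer events and less power, and the testosterone schedule in 11.1 dates recovery only coarsely.
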